#### Measures and Data Collection Procedures

Data from each IETP participant will be obtained from site leads beginning with Tampa (2015 to present; n=approximately 350). We will obtain identifiers that allow linkage to VA and DoD health system data and create a study crosswalk database behind the VA firewall that includes the encrypted identifier, a study ID, and contact information for interview and survey administration. We will obtain intake and discharge measures from each IETP site. We will assess IETP fidelity based on the IETP characterization table (Multimedia Appendix 1) using a checklist (Multimedia Appendix 2) and chart abstraction focusing on the admission note, admission IETP care plan, discharge TBI care plan, and discharge summary, which are highly accurate in describing the reasons for seeking treatment, baseline status, the type of treatment recommended, the type of treatment received, and outcomes on discharge (Multimedia Appendix 12).

We will also link these IETP data to VA and DoD health system data, as we have done previously [36], to obtain information on physical and mental health, medications, and military demographic data before and after IETP. As approximately 90% (225/250) of participants in the IETP are active duty at the time of treatment with the goal of returning to full duty and operational partner priority outcomes include return to duty or employment, the use of VHA data (eg, Patient Health Questionnaire-9 [PHQ-9] and PTSD checklist-5) is not a feasible approach to long-term outcomes. Therefore, we will conduct a survey using a VA-approved web-based survey software for participants of IETP (2015-2022; approximately 500) using a Modified Dillman Method, which we used in prior VA studies (Multimedia Appendix 13) [37-40]. We will begin a survey of earlier IETP graduates in the first year of the study and send surveys to new graduates 6-9 months post study completion. The final outcome measures included in the survey will be developed in collaboration with stakeholders. The current list of stakeholder-identified measures that are evaluated at intake and discharge include the PHQ-9, PTSD checklist-5, MPAI, and the Neurobehavioral Symptom Inventory.

We will also use VA and DoD health system data to describe health system outcomes such as use, new diagnoses, and adverse outcomes, which will, together with data baseline, discharge, fidelity, and discharge outcomes, be used to develop trajectories of recovery.

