#### Identify Components of IETP Associated With Sustainment and Improvement Trajectories

Outcomes currently identified by operational and clinical stakeholders that are collected at all sites (Tables 3 and 4) will be included in the survey to develop longitudinal outcome trajectories. On the basis of stakeholder feedback, we will also measure and describe community reintegration, employment, retention in the military where relevant, compliance to discharge from the TBI care plan, reasons for difficulty in care plan compliance, and unmet rehabilitation needs. Per operational partners’ request, we will also use VHA and DoD data to identify use relevant to discharge (eg, TBI care plan within primary, mental health, specialty care, or emergency care).

We will use Bayesian network analysis to generate a directed acyclic graph, which probabilistically describes the trajectory of symptoms, care, and outcomes for IETP participants. This network will enable us to explore the contribution of the baseline phenotype to the decision to use a particular treatment course and the contribution of those treatments to the participants’ resulting outcome measures [53]. Using a hill-climbing algorithm scored with the Bayesian information criterion, we will establish directional connections between nodes, called edges, and evaluate the robustness of the edges using bootstrapped samples of the data. We will a priori exclude any implausible directed edges (eg, IETP care cannot lead to precare symptoms). The resulting directed network will have edges between the levels: (1) phenotypes, (2) treatment, and (3) outcomes, while disallowing connections that go from levels 2 to 1 or 3 to 2 or 1. We can allow edges between nodes within the treatment level of the network to better understand the interactions between treatments and to assess how the treatments individually and in combination probabilistically affect patient outcomes. By fitting this model, we can isolate the most probable trajectories between TBI phenotypes and treatments and then determine which treatments have a higher probability of positive long-term outcomes. To gain an understanding of the treatment courses on outcomes, we will present a graphical display of the nodes and edges, the conditional probabilities calculated between nodes that estimate the probability of long-term outcomes given the participants’ IETP components and comorbidity phenotypes, and the robustness measures from bootstrapping.

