#### Power and Missing Data

The analyses in this aim take an exploratory approach to establishing phenotypes with latent variable mixture models and isolating common trajectories based on Bayesian networks. As such, we do not have a targeted hypothesis with which to power this analysis for minimum detectable effect sizes but rather a model selection approach using the Bayesian information criterion. With 500 participants, we expect that our sample size will be well above the number of nodes in the Bayesian network, which will allow for an accurate estimation of the conditional probabilities in the network [54,55].

We will assess the risk of bias owing to missing data by looking at patterns of missing measurements at each phase of the patients’ trajectories, although we expect most missingness to be postdischarge. Reasons for missing measurements will be tabulated with a focus on differentiating missed measurements for logistical reasons from dropouts or intermittent missingness potentially related to the condition of the patient. If >10% (25/250) of the patients have missing outcome measurements for any of the follow-up measures or if the comparisons of baseline characteristics between patients with missing and nonmissing measurements indicate considerable imbalances, rather than only looking at complete cases, we will apply the structural expectation-maximization algorithm, an imputation method that directly processes data with missing values while fitting the Bayesian network [56]. This method incorporates baseline and follow-up factors beyond the variable being analyzed to account for the dependence of missing data on other factors. TBI history is a primary piece of data required for admission to the program. It is unlikely that any data will be missing for TBI history. However, if >20% (>50/250) of the sample has missing data related to TBI history, the study should be stopped.

### Aim 3

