### Potential Limitations

The proposed PEI does not address implementation sustainment and cost. Implementation and cost evaluation elements are beyond the scope of this 3-year PEI; however, the proposed aims are foundational efforts that will facilitate a cost and sustainment evaluation after the proposed PEI. A “rigorous” design (eg, step wedge, randomized controlled trial) is not proposed. Our proposed mixed methods design is aligned with the preimplementation emphasis of operational requests and needs. There is a potential lack of clinician or administrator participation in aim 1. We partnered with coinvestigators at each study site to support recruitment. We will meet with them during “training time” or “clinical team meetings” to maximize their availability and convenience to participate. We will offer individual interviews (by phone or in person) to maximize participation for those unable to participate in the focus groups. We will conduct meetings in person or by phone to meet their preferences, particularly through individual interviews. All patients will be interviewed by phone. The time frame is compressed for study activities. For aim 1, we will conduct simultaneous site visits and rapid iterative analysis as data are collected and analyzed. Transcription turnaround time is minimized using an internal transcription service with an established protocol with the Tampa team. For aim 2, we will leverage existing data sets (i.e, IETP, TBI model systems, VA, and DoD data sets) and include site leads as experts in those data sets to facilitate timely analyses. A potential pitfall of aim 2 is the lack of participation in long-term outcome surveys; we will address this with an introductory letter from PM&R describing the importance of the study, as well as individualized follow-up strategies that have been effectively used by the team in previous projects. For aim 3, final report content development will begin at the onset of the PEI, supported throughout aims 1 and 2, relying on protocols and templates used in other projects. We will use an iterative design process that will support the development and validation of the content with the PEI stakeholder panel. There is no comparison group for this treatment modality. The operational partner did not want to prioritize this comparison and felt this would be better suited in subsequent proposals.

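### With post-discharge outcomes missing, structural EM makes the component-outcome edges depend on a starting graph that the plan does not fix or vary

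*Protocol article*

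**What the plan says.** Under the Aim 2 heading on components associated with sustainment and improvement trajectories, the protocol fixes the search: "Using a hill-climbing algorithm scored with the Bayesian information criterion, we will establish directional connections between nodes". Edges may run from phenotype to treatment to outcome but not backwards. The stability of edges is judged by bootstrapping the data.

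Under Power and Missing Data, the network is planned on this basis: "With 500 participants, we expect that our sample size will be well above the number of nodes in the Bayesian network". The protocol will look at where measurements are missing, "although we expect most missingness to be postdischarge". The trigger is "If >10% (25/250) of the patients have missing outcome measurements for any of the follow-up measures", or considerable baseline imbalance between patients with and without the measurement. Once it is met, "we will apply the structural expectation-maximization algorithm, an imputation method that directly processes data with missing values while fitting the Bayesian network". The only alternative mentioned is a complete-case analysis.

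Potential Limitations adds: "A potential pitfall of aim 2 is the lack of participation in long-term outcome surveys". No expected non-response rate is given. Neither section names a starting graph or restarts, or describes scoring each outcome on the patients who have it.

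**The concern.** Structural EM alternates two steps. It fills missing values from the current graph, then rescores candidate graphs on the filled data. In this network the missing values are expected mainly in the outcomes, which are end nodes. A patient with no outcome, and nothing observed downstream of it, carries almost no information about the probability of the outcome given its parents. The procedure still counts that patient's filled value in the score.

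- If a component-outcome edge is absent from the current graph, the filled outcomes are unrelated to that component. The contrast is diluted, and adding the edge becomes harder.
- If the edge is present, the filled outcomes reproduce it. It then looks better supported than the observed data justify, and keeping it becomes easier.

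Both states can sustain themselves, so the same data can yield different graphs from different starts. The bootstrap resamples patients. Unless the start is varied as well, every replicate inherits the same dependence, and an edge or an absence produced by the start can look robust.

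These edges matter. Aim 3 and the Conclusions use the results to decide which components to implement and which to withdraw. A diluted edge could count against a useful component, and a self-sustained false edge could protect an ineffective one.

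**Working it through.** **The plan's own figures.** The trigger of 25/250 is 10%, as printed. The protocol gives no edge-recovery figure, effect size or non-response rate, so there is nothing further to reproduce.

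**Inputs.** N = 500, BIC hill-climbing, outcomes last and missingness mainly after discharge all come from the protocol. The assumptions are: one binary component received by 50% of patients; a binary outcome with a 20-point difference (40% against 60%, so correlation φ = 0.2); outcomes missing completely at random; nothing observed downstream of the outcome; and 12%, 30% or 50% missing.

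**Thresholds.** Let f be the observed fraction and z the statistic for the edge among patients with the outcome, so z² ≈ fNφ². Adding one binary parent raises the log-likelihood by about Nφ²/2 and costs ½ ln N.

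- *Edge absent from the current graph.* Filling shrinks φ to fφ. The edge is added if N f²φ² > ln N, that is z > √(ln N / f).
- *Edge present in the current graph.* Filling repeats φ over all N. The edge is kept if Nφ² > ln N, that is z > √(f ln N).
- *Scoring only patients with the outcome.* The edge is included if z > √(ln(fN)).

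With ln 500 = 6.215:

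| Missing | Add | Keep | Observed-only | Expected z = 0.2√(fN) |
|---|---|---|---|---|
| 12% | 2.66 | 2.34 | 2.47 | 4.20 |
| 30% | 2.98 | 2.09 | 2.42 | 3.74 |
| 50% | 3.53 | 1.76 | 2.35 | 3.16 |

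**Detection of the true edge.** Taking z as normal with unit variance about its expected value:

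| Missing | Empty start | Start holding the edge | Observed-only | The two starts disagree |
|---|---|---|---|---|
| 12% | 94% | 97% | 96% | 3% |
| 30% | 78% | 95% | 91% | 17% |
| 50% | 36% | 92% | 79% | 56% |

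Direct simulation agrees. The empty start against observed-only scoring gave about 37% against 80% at 50% missing, 79% against 91% at 30%, and 94% against 97% at 12%. The two starts disagreed in 56%, 17% and 3% of data sets.

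**False edges at 50% missing.** A null edge already in the start survives with probability P(|z| > 1.76) ≈ 8%. Observed-only scoring admits it with probability P(|z| > 2.35) ≈ 2%.

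**Larger networks.** A simulated linear-Gaussian network had 8 components, 3 of them real, N = 500, and response depending on observed data. The share of real edges found was:

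| Missing | Empty start | All-edges start | Start from observed-patient graph | Observed-only |
|---|---|---|---|---|
| 12% | 0.89 | 0.94 | 0.92 | 0.92 |
| 25% | 0.74 | 0.91 | 0.85 | 0.85 |
| 40% | 0.51 | 0.91 | 0.81 | 0.81 |
| 60% | 0.06 | 0.84 | 0.59 | 0.59 |

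At 60% missing the all-edges start admitted 0.122 false edges per null component, against 0.031 for observed-only scoring. Without a downstream proxy, the empty and all-edges starts chose different parents for the outcome in 19%, 51%, 81% and 99% of runs at the four missing rates. With an observed post-outcome proxy (correlation 0.7, assumed), empty start against observed-only became 0.92 against 0.92, 0.84 against 0.86, 0.75 against 0.79, and 0.49 against 0.59.

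**Does the remedy work?** Running from both the empty graph and the observed-patient graph, and keeping the one with the better observed-data BIC, restored detection to 76–80%, with null edges at 1.5–2%.

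**The case against.** The strongest reply is that a starting graph and restarts are algorithm settings, which a condensed article may leave to the analysis plan. That stands as far as omission goes, and silence about the start is not in itself the point. What the article does fix is the combination: BIC search, outcomes last, structural EM as the remedy, and a bootstrap as the stated robustness check. Nothing in the bootstrap as described varies the start, so it would not reveal this dependence.

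A reader might infer that structural EM usually loses more real edges than scoring observed patients, or that the plan's default hides useful components. The documents do not support either. They name no empty start. The loss belongs to that start. In the linear-Gaussian network a dense start keeps more real edges and errs by admitting false ones, and a start from the observed-patient graph loses none.

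The simple network above is also less informative than the planned one. Tables 3 and 4 list four survey measures as well as post-program diagnoses, health care use and medications from VA and DoD records, which do not depend on survey response. The protocol says the method draws on follow-up factors, and it does not expressly forbid edges between outcomes. The proxy results show that this narrows the empty-start gap, though at 60% missing it does not close it.

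Replacing structural EM outright with response-weighted scoring is not supported either. At 50% missing, raw inverse-probability weights, which sum to about 500, admit a null edge about 11% of the time. The figures are 2% unweighted and 3% with normalised weights. Raw weighting recreates the fault of counting respondents as extra patients.

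**Conclusion.** The point holds in a limited form. With outcomes missing as end nodes, structural EM under BIC hill-climbing has self-reinforcing solutions, so the component-outcome edges depend on a start that the plan neither states nor varies. The direction of harm depends on the start: lost real edges from an empty graph, retained false edges from one that already holds them.

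The size runs from slight near the 10% trigger (the two starts disagree in 3% of data sets at 12% missing) to serious at 50% (56%), when no observed post-discharge variable informs the outcome. It is smaller when one does. Effect size, number of components and missing rates are all assumptions. The trigger is likely to be met, since the protocol itself names survey non-participation as a pitfall, but no document figure establishes by how much. The analysis is described as exploratory. Its results nevertheless feed decisions on components, so a cheap safeguard is worthwhile.

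**What to change.** Keep structural EM and add the following to the missing-data plan:

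1. Run it from at least two starts: an empty graph, and the graph fitted to patients with each outcome observed. Select between the results by BIC computed on the observed data.
2. Vary the starting graph within the bootstrap, so that edge robustness reflects it.
3. Report every component-outcome edge that changes between starts.
4. As a sensitivity analysis, score edges into each survey outcome on the patients who have that outcome. If response weights are used there, normalise them to sum to the number of respondents, so that BIC does not treat respondents as extra patients.

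The cost is modest: some added computation and reporting, plus a response model on data already being linked if weights are used. No new data collection is needed.

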#### Overview

We will use qualitative methods to describe and characterize IETP to support implementation efforts across all 5 TBI-COE. In alignment with the QUERI Implementation Roadmap, this project will coconstruct a meaningful theoretical context for identifying and describing the implementation of each IETP using the Consolidated Framework for Implementation Research (CFIR) [28,29]. In addition, project leadership will use an implementation evaluation process conducted in a *sister* project, Optimizing Rehabilitation Interventions (ORION) for Cognition Following Complex Traumatic Brain Injury funded by the DoD (W81XWH-19-1-0615), which will maximize the efficiency of this effort and promote interoperability and knowledge translation between VA and DoD. The PEI team will use this implementation evaluation process to present and review the content in initial development in Tampa. Subsequently, the materials will be used and further developed in an iterative fashion at the other IETP sites. The aim 1 deliverable is a characterization of the IETP, IETP Care Implementation Elements Inventory, and IETP Logic Model. The inventory and logic model will be iteratively developed and used to assess the implementation at TBI-COE sites.

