#### Characterize IETP Participants

We will begin characterization with the Tampa site (n=approximately 350) and Richmond site (n=approximately 150), followed by other sites. We will use VA and DoD health system data to characterize preadmission military and sociodemographic characteristics, TBI-related diagnoses (eg, PTSD, pain, and sleep), and medication use (eg, opioids, antidepressants, and sedative hypnotics). We will add data from TBI history and symptom inventories administered at IETP admission to develop mild TBI phenotypes [36,41,42]. This allows the characterization of participants in the IETP and the identification of groups that are likely to have similar courses of care.

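### The rule to stop the whole study if TBI history is missing in more than 20% of the sample is broader than the Aim 2 analyses that use TBI history, and it has no stated check time

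*Protocol article*

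**What the plan says.** All references are to the protocol article.

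- **The rule.** Power and Missing Data (Aim 2) sets the threshold as "However, if >20% (>50/250") and the consequence as "of the sample has missing data related to TBI history, the study should be stopped". The sentence does not confine the stop to Aim 2, and it does not say when or by whom the check is made. Just before it, the section notes that TBI history is needed for program admission and is unlikely to be missing.
- **Where TBI history is used.** Characterize IETP Participants: "We will add data from TBI history and symptom inventories administered at IETP admission to develop mild TBI phenotypes". It joins military and sociodemographic characteristics, diagnoses and medication use from VA and DoD data. The phenotypes then form the first level of the Bayesian network described in the section on IETP components and trajectories.
- **What does not use it.** Aim 1, Overview: "We will use qualitative methods to describe and characterize IETP to support implementation efforts across all 5 TBI-COE". Under Sampling and Sample Size, patient interviewees are chosen by top or bottom quartile of the discharge MPAI.
- **Treatment of other missing data.** For outcomes, the plan has an analytic fallback: "If >10% (25/250) of the patients have missing outcome measurements for any of the follow-up measures", or if baseline imbalances are considerable, it applies structural expectation-maximization, "an imputation method that directly processes data with missing values while fitting the Bayesian network".
- **Order of data.** "We will begin characterization with the Tampa site (n=approximately 350) and Richmond site (n=approximately 150), followed by other sites".

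**The concern.** A stopping rule should reach only as far as the problem that triggers it. This one is triggered by a gap in one input to one model, but its stated consequence covers the whole evaluation.

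What would be lost is whatever work remains when the rule fires. That could include staff, DoD and patient interviews, site observation, outcome surveys of graduates, and the Aim 3 products built on the qualitative work. None of these analyses takes TBI history as an input. Most of the TBI history records already exist in program files, so stopping is not a way to avoid collecting them.

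Without a check time, the rule could be applied to the first site's file, to the pooled sample, or at the end. These can give different answers, because one site makes up most of the stated sample.

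**Working it through.** **1. Reproduce the printed figures.** 50/250 = 20.0% and 25/250 = 10.0%. Both percentages are right on a denominator of 250.

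**2. Compare with the Aim 2 sample.** The same section says: "With 500 participants, we expect that our sample size will be well above the number of nodes in the Bayesian network". That matches Tampa plus Richmond: 350 + 150 = 500. On 500:
- 20% is 0.20 × 500 = 100 patients, so the percentage rule triggers at 101.
- The printed count of more than 50 triggers at 51, and 50/500 = 10.0%.

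The percentage and the count therefore give different triggers on the stated sample, and both are carried forward.

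**3. Can one site trigger the rule?** Take Tampa at 350, with every other record complete (assumed):

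| Reading of the threshold | Missing records needed | Share of Tampa records |
|---|---|---|
| More than 20% of 500 | 101 | 101/350 = 28.9% |
| Printed count, more than 50 | 51 | 51/350 = 14.6% |

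If other sites bring the total above 500, the first share rises and the second does not change.

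**4. How likely is a trigger?** The documents give no expected rate of missing TBI history, so the rates below are assumptions. Each entry is an exact binomial upper tail, treating records as independent.

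| Assumed true missing rate | P(>50 of 250) | P(>100 of 500) | P(>50 of 500) |
|---|---|---|---|
| 5% | 1 × 10⁻¹⁷ | 5 × 10⁻³³ | 2 × 10⁻⁶ |
| 10% | 7 × 10⁻⁷ | 8 × 10⁻¹² | 0.46 |
| 15% | 0.013 | 0.001 | 0.999 |
| 20% | 0.46 | 0.47 | >0.999 |

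If missingness is as rare as the protocol expects, the 20% rule does not fire. A fault shared across one site's records would break the independence assumption, so step 3 is the more relevant scenario.

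**5. What depends on TBI history?**

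| Component | Uses TBI history? |
|---|---|
| Aim 1 interviews, focus groups, site observation | No |
| Aim 2 phenotype model | Yes, as one of several inputs |
| Aim 2 Bayesian network | Yes, through the phenotypes |
| Aim 2 description of survey outcomes (symptom scales, employment, reintegration) | No |
| Aim 3 products from Aim 1 (such as the elements inventory, logic model, patient experience summaries) | No |
| Aim 3 content from phenotypes and trajectories | Yes, indirectly |

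The rule stops every row, but only the rows marked yes are affected by the missing input.

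**The case against.** **The sentence may mean Aim 2 only.** It sits in an Aim 2 section that opens by referring to the analyses in that aim, and the article uses the word study loosely elsewhere. Its wording advises a stop and does not describe an automatic trigger. Communication and Collaboration also lets the investigators rework activities with the operational partner. This is a fair reading of intent, but the text does not state the limit, and general flexibility does not amend a specific rule.

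**A hard limit may be reasonable.** TBI history is required for admission. If more than a fifth were missing, one could doubt the linkage or whether the cohort is the intended one. Patient interview contacts also come from Aim 2 data. This stands as a reason to query the site and withhold the phenotype results. It gives no reason to end staff and DoD interviews, and the protocol does not offer this rationale.

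**The outcome fallback is not a direct precedent.** Structural expectation-maximization works inside the network, whereas TBI history enters earlier, in the mixture model. Handling them differently is therefore not a contradiction. It remains true that the section gives an analytic fallback for outcomes and none for this input.

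**Stronger readings that the documents do not support.**
- *That two whole aims are independent of TBI history.* Aim 3 triangulates Aims 1 and 2, so part of it depends on the phenotypes.
- *That the rule can fire only once all data are in.* Files arrive site by site, starting with Tampa, so missingness could be seen early. The supported point is that no check time is stated.
- *That all interviews and surveys would be forfeited and no aim answered.* Nothing says collected data would be discarded. The Results section reports staff groups complete at 4 of 5 sites and DoD and patient interviews under way at all 5.

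**Conclusion.** The point holds in a limited form. The stopping rule is wider than the analyses that need TBI history, and its timing is not fixed. If it fired and were followed literally, it would end remaining Aim 1 work, the remaining survey work and the Aim 3 products based on Aim 1, none of which this missingness affects.

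A single large site could cause it, at 28.9% of Tampa records on a sample of 500 or 14.6% on the printed count. Both figures assume complete records elsewhere and about 350 at Tampa. The protocol expects almost no missing TBI history, so the chance of harm is low. This is an inexpensive improvement to the wording and does not threaten the evaluation's validity as it stands.

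**What to change.** Replace the stopping sentence with text along these lines:

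> If TBI history is missing for more than 20% of the Aim 2 sample, the phenotype model will be fitted without TBI history, with a secondary fit in the patients or sites where it is recorded, and results that depend on the phenotypes will be labelled accordingly. Aim 1, the survey and the Aim 3 products not based on phenotypes will continue. Missing TBI history will be checked when each site's file arrives and queried with the site lead.

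State the denominator to which the 20% applies, because the printed count and the sample of 500 give different triggers.

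The cost is a short change to the text and one tabulation per site file. The downside is that, if the rule triggers, the main phenotypes may be less specific to TBI. The secondary fit and the labelling make that visible.
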